#### International Consultation on Incontinence Questionnaire—Short Form (ICIQ-SF)

ICIQ-SF consists of four questions assessing the frequency, severity, and impact of UI, along with a set of eight self-diagnostic items that evaluate the causes or situations of UI experienced by patients. Only the first three questions are scored, and the total score ranges from zero to twenty-one points. The impact of UI on QoL is divided into: no impact (0 points); mild impact (1 to 3 points); moderate (4 to 6 points); severe (7 to 9 points), and very severe (10 or more points) [40].

#### International Consultation on Incontinence Questionnaire Overactive (ICIQ-OAB)

ICIQ-OAB was developed to specifically assess urinary symptoms related to Overactive Bladder Syndrome (OAB), through four questions related to frequency, nocturia, urgency, and incontinence. The ICIQ-OAB generates an overall score ranging from 0 to 16 points, reflecting the impact on the patient’s QoL. Each question includes a scale ranging from 0 (no discomfort) to 10 (very uncomfortable) to measure the level of symptom discomfort [41].

#### Pelvic Floor Distress Inventory (PFDI-20)

PFDI has 20 questions divided into 3 domains (bladder/intestine/pelvis) in their sub-scales: Pelvic Organ Prolapse Distress Inventory (POPDI-6), Colorectal-Anal Distress Inventory (CRADI-8), and Urinary Distress Inventory (UDI6). The first question raised is the presence or absence of the symptom described in each question. If the response is positive, there is quantification of the symptom, where the patient has options: "not at all"/"a little"/"moderately"/"quite a bit". The response options are quantified from zero (no symptoms) to 4 (significant impact of the symptom). The average of the total scores per sub-scale is multiplied by 25 and finally, the three scores are summed [42].

#### World Health Organization Quality of Life (WHOQOL)

The WHOQOL questionnaire assesses four domains to evaluate quality of life (QoL): physical, psychological, social relationships, and environment. Responses are rated on a Likert-type scale, ranging from 1 to 5, where higher scores indicate a higher QoL. To calculate the final score, responses from each domain are summed and divided by the number of questions within that domain, resulting in the following classification: needs improvement (1 to 2.9); fair (3 to 3.9); good (4 to 4.9); very good (5) [43].

#### Female Sexual Function Index (FSFI)

FSFI has 19 questions grouped into six domains: desire, arousal, lubrication, orgasm, satisfaction, and pain. All questions are multiple-choice, and each answer is assigned a value from 0 to 5. Scores are calculated by a mathematical formula, resulting in a sexual function score ranging from 2 to 36 points, with a cutoff point of 26.5 points. A lower score indicates poorer sexual function, and a score equal to or below this point indicates sexual dysfunction [44].

#### Patient Global Impression of Change (PGI-C)

The PGI-C is a 7-item scale ranging from "1 = no change" to "7 = very much better," where the patient can broadly evaluate their improvement throughout the treatment, involving personal and psychometric aspects inherent to the treatment process [45].

### Sample size

The sample size was pre-determined using G-Power 3.1.9.2 (F-tests—ANOVA: repeated measures, between groups), based on a previous study [46] utilizing vaginal manometry data. The sample size was estimated with a significance level of 0.05, power of 98%, and effect size of 0.23. According to this methodology, the sample size resulted in 27 participants. An additional 20% for possible losses (5 volunteers) was added. Thus, 32 volunteers will be recruited and randomized into two groups of 16 participants each.

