### Statistical analysis

Data will be analyzed using the Statistical Package for Social Science (SPSS) version 22.0, and will be used Excel Software version 2019 to capture the data. Initial analysis will present sociodemographic and clinical parameters in descriptive tables showing mean values, standard deviation, frequency, medians, and percentiles. Additionally, 95% confidence intervals will be presented. To assess initial group differences, unpaired t-test or Mann-Whitney test will be used for continuous variables, and chi-square test for categorical variables. Depending on data normality, repeated measures ANOVA or Kruskal-Wallis test followed by Tukey post-test will identify differences. Time-group interaction and intra-group variations for studied variables will be analyzed. Mauchly test will check sphericity, and if violated, Greenhouse-Geisser correction will be applied. Effect size (Cohen’s f2) and statistical power will also be calculated. Significance level of 5% will be considered.

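### The stated 98% power at 27 participants does not follow from the stated test and effect size, whatever non-negative between-visit correlation is assumed

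*Protocol article*

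**What the plan says.** The Sample size section names the software and procedure as "G-Power 3.1.9.2 (F-tests—ANOVA: repeated measures, between groups", and takes its data from an earlier vaginal manometry study. It continues: "The sample size was estimated with a significance level of 0.05, power of 98%, and effect size of 0.23". The result is given as "the sample size resulted in 27 participants", and then "An additional 20% for possible losses (5 volunteers) was added", which makes 32 women in two groups of 16.

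Three other places matter:

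- The Results section sets three assessments (baseline, end of treatment, one month later) and makes manometry pressure the primary outcome.
- The Statistical analysis section says "Time-group interaction and intra-group variations for studied variables will be analyzed". It also names Cohen's f² as the effect size to be calculated from the trial's results.
- Neither the correlation between visits nor the metric of the 0.23 is given anywhere.

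**The concern.** For a between-groups F test, 0.23 as Cohen's f is a fairly small effect, and 27 people are few for it. Repeated measurement does not close that gap: when visits are positively correlated, averaging over three of them adds less information than three independent readings would. A claim of 98% on these inputs therefore needs checking.

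This is the trial's only sample-size justification, and it concerns the primary outcome. Readers are told that an effect of the planned size would be missed 2% of the time. If that is far too low, a null result would be taken as stronger evidence of no effect than it is. In addition, the power is quoted for the between-groups effect, while the analysis section looks to the time-group interaction. These are different F tests, and they respond to the correlation in opposite directions.

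**Working it through.** **Inputs.** Alpha 0.05, effect size 0.23, N = 27, k = 2 groups (Sample size); m = 3 assessments (Results). Two inputs are assumed: 0.23 is Cohen's f, which is the input G*Power takes for this test, so f² = 0.0529; and the between-visit correlation ρ is varied from 0 to 1.

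**Trying to reproduce 27 at 98% with the named test.** The between-groups effect has

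λ = f²·N·m / (1 + (m − 1)ρ), with 1 and N − 2 degrees of freedom,

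and power is the probability that a noncentral F with that λ exceeds the 5% critical value.

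- ρ = 0: λ = 0.0529 × 27 × 3 / 1 = 4.28; power 51%.
- ρ = 0.5: λ = 4.28 / 2 = 2.14; power 29%.
- ρ = 1 (limit): λ = 4.28 / 3 = 1.43; power about 21%.

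| ρ | Power, N = 26 | Power, N = 27 | Power, N = 32 | Total N for 98% |
|---|---|---|---|---|
| 0 | 50% | 51% | 59% | 104 |
| 0.5 | 28% | 29% | 34% | 205 |
| 0.7 | 24% | 25% | 29% | 246 |
| 0.9 | 21% | 22% | 26% | 287 |

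The stated figure is not reproduced. Power falls as ρ rises, so ρ = 0 is the most favourable non-negative value, and it gives 51%. Changing the number of visits does not help: at ρ = 0 and N = 27, two visits give 37% and four give 63%. For 98% at N = 27 with three visits, f would have to be 0.46 (ρ = 0) or 0.66 (ρ = 0.5).

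**Readings that do reach 27.**

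*Time-group interaction, f = 0.23.* Here λ = f²·N·m / (1 − ρ), with 2 and 2(N − 2) degrees of freedom. At N = 27 and ρ = 0.79, λ = 4.28 / 0.21 = 20.4 and power is 98%.

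| ρ | Power, N = 26 | Power, N = 27 | Total N for 98% |
|---|---|---|---|
| 0.5 | 70% | 72% | 62 |
| 0.7 | 91% | 92% | 38 |
| 0.8 | 98% | 98.6% | 26 |

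*Named test, 0.23 as f²* (f = √0.23 = 0.48). At ρ = 0.02, λ = 0.23 × 27 × 3 / 1.04 = 17.9, and 27 is the smallest N giving 98%. At N = 27, power is 98.6% at ρ = 0, 83% at 0.5 and 76% at 0.7. At ρ = 0.5, 98% needs 49.

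*Named test, 0.23 as partial eta²* (f² = 0.23 / 0.77 = 0.299, f = 0.547). At ρ = 0.17, λ = 0.299 × 27 × 3 / 1.34 = 18.1, and 27 is again the smallest N giving 98%. At ρ = 0.5, 98% needs 38.

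**Losses.** 20% of 27 is 5.4, and 27 + 5 = 32, so the figure follows the stated method. But 32 × 0.8 = 25.6, so a 20% loss leaves about 26 completers, not 27. Dividing instead, 27 / 0.8 = 33.75, or 34.

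**The case against.** The strongest reply is that the article may describe a sound calculation badly. It writes only "effect size of 0.23", with no metric, and the one effect-size metric it names anywhere is Cohen's f², in the Statistical analysis section. The time-group interaction, which that section does analyse, gives 27 at a correlation near 0.79. The fault may then be a mislabelled procedure or metric, and the source study that would settle this is not at hand.

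Much of that stands. A reader might infer from the table that this trial has 29% power. The documents do not support that: 29% needs both 0.23 as f and a correlation of 0.5, and neither is stated. A reader might also infer that 27 can come only from a different test. That is wrong too, since the named test gives 27 under the f² and partial eta² readings at low correlations. Nor is the loss allowance an error against its own description, and the odd total of 27 does not matter because 32 splits evenly.

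What the reply does not do is rescue the sentence as printed. Each alternative needs a test, a metric or a correlation that the sample-size paragraph does not give. Each is also fragile: at a correlation of 0.5 the interaction has 72% power at 27, and the f² reading has 83%.

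**Conclusion.** The point holds in a limited form. With 0.23 as Cohen's f, two groups and three visits, the named between-groups test has about 21% to 51% power at 27 participants over all non-negative correlations, and 98% needs at least 104. On that reading the planned effect would be missed in about 49% to 79% of trials, not 2%. The conclusion depends on reading 0.23 as f. It does not depend on any particular value of the correlation.

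It does not follow that the trial is badly underpowered. The article does not settle which test, metric and correlation were used, so its actual power cannot be fixed from the documents. There is a second, linked defect: the power is stated for the between-groups effect while the analysis section turns to the time-group interaction, so a reader cannot tell which test the 98% belongs to. The loss allowance is only a side note. The power statement should be corrected before results are interpreted against it.

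**What to change.** Keep 32 participants and rewrite the Sample size paragraph:

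- Name the primary test. If it is the time-group interaction, power that test, and make the Sample size and Statistical analysis sections agree.
- State the effect-size metric, the three visits, and the assumed between-visit correlation with its source.
- Replace 98% with the power that about 26 completers give for that test over a range of correlations. With f = 0.23 this is 50% (correlation 0) and 28% (0.5) for the between-groups test, or about 70% (0.5) to 98% (0.8) for the interaction. If another metric was meant, recompute on it.
- Say that a 20% loss from 32 leaves about 26 completers.

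The cost is one paragraph and no extra participants. The downside is that the stated power becomes less favourable.

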### Recruitment

It will be a randomized, controlled, parallel, and blinded clinical trial, with recruitment of volunteers from June 01, 2023 to June 30, 2024. The sample will consist of users from the general gynecology outpatient clinic of the MEJC who present SUI and a diagnosis of stage I or II cystocele.

### Randomization, allocation concealment, and blinding

The randomization process will be carried out electronically through the website http://www.randomization.com to assign each participant to the PFMT or CG. Allocation will be 1:1, and each participant will have an equal probability of belonging to either group. Two pieces of information will be entered: the sample size and the number of groups. Website will generate specific coding for each group and will distribute subjects randomly. To ensure blinding in this study, the processes of randomization, assessment/reassessment, training of selected volunteers, and data analysis will be performed by distinct researchers.

### Data collection

Data will be collected at the MEJC, Brazil.

### Statistical analysis

Data will be analyzed using the Statistical Package for Social Science (SPSS) version 22.0, and will be used Excel Software version 2019 to capture the data. Initial analysis will present sociodemographic and clinical parameters in descriptive tables showing mean values, standard deviation, frequency, medians, and percentiles. Additionally, 95% confidence intervals will be presented. To assess initial group differences, unpaired t-test or Mann-Whitney test will be used for continuous variables, and chi-square test for categorical variables. Depending on data normality, repeated measures ANOVA or Kruskal-Wallis test followed by Tukey post-test will identify differences. Time-group interaction and intra-group variations for studied variables will be analyzed. Mauchly test will check sphericity, and if violated, Greenhouse-Geisser correction will be applied. Effect size (Cohen’s f2) and statistical power will also be calculated. Significance level of 5% will be considered.

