### Results

All assessments will be conducted by a blinded evaluator. The volunteers will undergo initial evaluation, including medical history, gynecological examination, functional assessment of the PFM, and questionnaires. The assessments will take place at three time points: before treatment (baseline assessment), at the end (final assessment), and one month after the last session (re-assessment). Fig 7 illustrates the assessment and re-assessment items.

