**Fig 7 pone.0308701.g007:**
[figure not shown]
Assessment and re-assessment items. **Note:** ICIQ-SF—International Consultation on Incontinence Questionnaire; ICIQ-OAB—International Consultation on Incontinence Questionnaire Overactive; PFDI -20—Pelvic Floor Distress Inventory; WHOQOL-bref—World Health Organization Quality of Life; FSFI—Function Sexual Female Index; PGI-C—Patient Global Impression of Change.

The primary outcome will be PFM pressure measured by vaginal manometry. Secondary outcomes will include manual muscle strength testing (Modified Oxford Scale) and questionnaires: International Consultation on Incontinence Questionnaire—Short Form (ICIQ-SF), International Consultation on Incontinence Questionnaire Overactive (ICIQ-OAB), Pelvic Floor Distress Inventory (PFDI-20), World Health Organization Quality of Life (WHOQOL), Female Sexual Function Index (FSFI), and Patient Global Impression of Change (PGI-C).

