#### Manual muscle strength testing

The evaluator performs bidigital palpation and instructs the volunteer to contract the PFM with the command "squeeze my finger with maximum force you can." It is necessary for the volunteer not to associate PFM contraction with accessory muscles. Muscle strength is graded according to the Modified Oxford Scale [39], which classifies muscle strength into six grades, from grade 0 to 5.

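### If normality is rejected, the plan falls back on Kruskal-Wallis with Tukey, which cannot deliver the time-group interaction or within-group analysis it promises for outcomes measured three times per woman

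*Protocol article*

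**What the plan says.** The Results section of the protocol article names the primary endpoint: "The primary outcome will be PFM pressure measured by vaginal manometry". It sets the visits: "The assessments will take place at three time points: before treatment (baseline assessment), at the end (final assessment), and one month after the last session". The Sample size section gives the layout: "32 volunteers will be recruited and randomized into two groups of 16 participants each".

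The Statistical analysis section then chooses the test: "Depending on data normality, repeated measures ANOVA or Kruskal-Wallis test followed by Tukey post-test will identify differences". The next sentence states what the analysis must deliver: "Time-group interaction and intra-group variations for studied variables will be analyzed". Mauchly's test and the Greenhouse-Geisser correction follow, and these belong to the ANOVA branch only. Mann-Whitney is named only for comparing the groups at baseline.

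The sentence on the choice of test is not limited to one outcome. It therefore also governs secondary outcomes such as the Modified Oxford Scale, which "classifies muscle strength into six grades, from grade 0 to 5".

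**The concern.** The plan treats Kruskal-Wallis as the rank counterpart of repeated measures ANOVA. It is the counterpart of one-way ANOVA on independent samples. Three values from one woman are not independent, and a one-way test has no term for the difference between arms in change over time, which is the question of the trial.

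The branch could well be used. Pressure may be skewed, and a six-grade ordinal scale is unlikely to look normal. The analyst would then either report a test that does not answer the promised question, or pick a different one after seeing the data.

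**Working it through.** **Inputs from the protocol article.** Two arms of 16 (Sample size); 3 visits per woman (Results); 5% significance level (Statistical analysis). The plan gives no operating figure for the fallback, so there is none to reproduce.

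**Assumptions.** The between-visit correlation rho is not stated. I take 0.5 to 0.7 as the main range, with 0.3 to 0.9 as a wider check. Data are simulated as normal or lognormal with equal correlation between visits.

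**What the test can address.** Kruskal-Wallis pools all N values, ranks them and computes H = 12/[N(N+1)] × Σ(R_j²/n_j) − 3(N+1), where R_j is the rank sum of sample j. H is referred to chi-square with k − 1 degrees of freedom, on the premise that the N values are independent. The formula contains neither the woman nor a group-by-time term.

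**Possible applications, 16 per arm, nominal 5%.**

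| Application | What is true | Rejection rate |
|---|---|---|
| Three visits within one group | no change | 0.4–0.8% (rho 0.5); 0.1% (rho 0.7) |
| Six group-by-visit cells | no change, no group effect | 3–5% |
| Six group-by-visit cells | both arms improve by 0, 0.25, 0.5 SD | about 16% (rho 0.7) |
| Six group-by-visit cells | both arms improve by 0, 0.5, 0.5 SD | 23–25% (rho 0.7); about 27% (rho 0.5) |
| Visits pooled by group | no group effect | about 17% (rho 0.5); 20–21% (rho 0.7) |
| Two arms at one visit | no group effect | 4.0–5.4% |
| Two arms on change from baseline | no group effect | 4.0–5.1% |

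**Approximate check by hand.**

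- *Across visits.* Only the within-woman share 1 − rho of the variance separates the visits, so H is about (1 − rho) times a chi-square with 2 degrees of freedom. The rejection rate is then about 0.05^(1/(1 − rho)). At rho 0.5 this is 0.05² = 0.25%. At rho 0.7 it is 0.05^3.33, below 0.01%. The simulated rates are a little higher in these small samples, but also far below 5%.
- *Pooled by group.* The variance of a group mean is 1 + 2·rho times what the test assumes: 2.0 at rho 0.5 and 2.4 at rho 0.7. The false-positive rate is about P(|Z| > 1.96/√2.0) = P(|Z| > 1.386) = 16.6%, and P(|Z| > 1.96/√2.4) = P(|Z| > 1.265) = 20.6%. Both agree with the table.

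**Wider range of rho (lognormal data).** Within a group, the null rejection rate is 2.0% at rho 0.3 and falls to practically zero at 0.8 and above. Pooled by group, it runs from 12% at rho 0.3 to 24% at 0.9. The direction does not change.

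**Cost in power within a group.** With lognormal data and a shared improvement of 0.8 SD on the log scale at both follow-ups, Kruskal-Wallis across visits had power of about 0.58 at rho 0.5 and at rho 0.8. Friedman's test had 0.80 and 0.99. With this larger trend, the six-cell test rejected 80–84% of the time although the arms did not differ.

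**The case against.** The strongest reply is that the plan does not say what Kruskal-Wallis is applied to, and that valid uses exist. With two arms it is equivalent to the two-sided Mann-Whitney test. On change from baseline it is a rank test of the group-by-time contrast and holds its size. This stands, and it rules out saying that the test must fail. It does not rescue the text: that use is not stated, a two-sample comparison needs no post-test, and it would still leave the within-group analysis without a method.

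Three stronger readings are tempting, and the document supports none of them.

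- **That the primary analysis is invalid.** The fault arises only if normality is rejected. Repeated measures ANOVA tests the interaction and is not touched by it.
- **That the trial carries a false-positive rate of 17% to 21%.** That figure belongs to pooling visits by group, which the plan does not describe. Across visits the test is conservative. The six-cell figures are not false-positive rates of Kruskal-Wallis itself, since its null is false when there is a shared trend; they show that a significant result would not mean a treatment effect.
- **That Tukey after a rank test is a definite error.** The sentence can be read as attaching Tukey to the ANOVA branch, and Tukey-type comparisons on ranks (Nemenyi) exist. The wording is ambiguous and needs clearing up.

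Choosing a test by a normality check in small groups is a separate question, not quantified here.

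**Conclusion.** The fallback is wrong as written, on a conditional branch. An independent-samples one-way test is named for three measurements per woman. Across visits or group-by-visit cells it cannot deliver the interaction or the within-group analysis promised in the next sentence. This is a stated rule that does not fit the design, not a detail left to an analysis plan.

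The likeliest harm is an unanswered treatment question and lost power within groups. A significant result that reflects only a shared time trend is also possible. Sizes, for 16 per arm and assumed rho of 0.5 to 0.7: under 1% rejection across visits; about 16% to 27% over the six cells for a shared trend reaching 0.5 SD; about 17% to 21% under the undescribed pooling. The document gives neither rho nor a trend, so these figures illustrate the error and do not predict it.

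**What to change.** In the Statistical analysis section, replace the Kruskal-Wallis and Tukey clause with a fallback that respects the design:

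- **Group-by-time question:** Mann-Whitney between arms on change from baseline at each follow-up, or rank ANCOVA, or a permutation test of the group effect. Name one.
- **Within-group change:** Friedman's test, followed by paired Wilcoxon tests with a multiplicity correction.
- **Modified Oxford Scale:** the same rank approach, because the grade is ordinal.
- **PGI-C:** Mann-Whitney between arms, because it has no baseline value.
- **Tukey-type comparisons:** keep them to the ANOVA branch.

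Replacing the main repeated measures ANOVA with ANCOVA or a mixed model is optional and not needed to correct this error. The cost is a few lines of analysis wording, with no extra patients, visits or data.

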**Methods:**

This study will be a randomized, controlled, parallel, and blinded clinical trial. The final sample will consist of 32 women diagnosed with SUI and cystocele (stage I and II). All volunteers will be assessed and reassessed using the same protocol: assessment form, gynecological examination, functional evaluation of PFM, and questionnaires to assess quality of life, urinary function, and sexual function. All volunteers will be evaluated for satisfaction levels post-treatment. The intervention will be PFMT, totaling 16 sessions to be conducted twice a week. Reevaluation will take place at the end of treatment and 1 month after completion of PFMT. Descriptive analysis and repeated measures ANOVA will be used for result analysis. A significance level of p<0.05 will be considered for all statistical tests.

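### A normality check on the collected data chooses between two tests that answer different questions, so the test of the primary outcome is not fixed in advance

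*Protocol article*

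**What the plan says.** The Statistical analysis section of the protocol article gives one rule for testing outcomes: "Depending on data normality, repeated measures ANOVA or Kruskal-Wallis test followed by Tukey post-test will identify differences". It does not name a normality test, a cut-off, or the values to be checked. The next sentence adds, with no condition attached: "Time-group interaction and intra-group variations for studied variables will be analyzed". The significance level is 5%.

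The Results section defines the primary endpoint: "The primary outcome will be PFM pressure measured by vaginal manometry". Nothing in the analysis section takes this endpoint out of the rule. The same Results section sets the visits: "The assessments will take place at three time points: before treatment (baseline assessment), at the end (final assessment), and one month after the last session".

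The abstract mentions only one of the two branches: "Descriptive analysis and repeated measures ANOVA will be used for result analysis". One secondary outcome, the Modified Oxford Scale, is ordinal by construction: "which classifies muscle strength into six grades, from grade 0 to 5".

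**The concern.** The rule reads the outcome data first and picks the test afterwards. This would matter little if both tests addressed the same question, but they do not. Repeated measures ANOVA uses all three visits and tests whether the arms change differently over time. Kruskal-Wallis compares independent groups on a single value per woman and has no time-by-group term. If the check sends manometry down the second branch, the interaction promised in the next sentence has no test attached to it.

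What is at stake is which comparison counts as the trial's primary result. Two analysts following the text could report different tests of different quantities from the same data, and a reader could not tell beforehand which was meant to decide. For an ordinal scale such as the Oxford grade, the measurement scale should settle the method, not the outcome of a normality check.

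**Working it through.** The plan gives no figure on this point to reproduce. The check asks how often the rule would switch, and what a switch would do.

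**Inputs from the protocol article:** 16 women per arm (Sample size); 3 visits (Results); 5% significance level (Statistical analysis).

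**Assumptions, because the document is silent:** Shapiro-Wilk at 5% as the check; within-woman correlation 0.3 to 0.8, the same between all visits; an illustrative effect of 0.7 SD at both follow-ups; Kruskal-Wallis applied to end-of-treatment values. The plan does not say which values it would be applied to.

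**Step 1. Switching when the data are truly normal.**
- One check: 5% by construction.
- Any of 2 × 3 = 6 group-by-visit cells, if independent: 1 − 0.95^6 = 26.5%. Simulation with correlated visits gives 24-27%.

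The choice of check alone therefore moves the switch rate about fivefold. With mild skew (lognormal, log-SD 0.3) and 16 per arm, the simulated rate is about 19% for one cell, 38% for one visit with the arms pooled, and 71% for any of six cells.

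**Step 2. Does the check protect the ANOVA?** The interaction F test has (2 − 1)(3 − 1) = 2 and 2 × 15 × 2 = 60 degrees of freedom. Under clearly skewed data (lognormal, log-SD 0.5, correlation 0.7), its simulated type I error is about 4.8% with 16 per arm and 4.7% with 13. In this setting the check protects against very little.

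**Step 3. Type I error of the whole procedure.** Under no effect and normal data, checking six cells and then running the selected test rejects in about 4.6-5.5% of runs.

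**Step 4. Power of each branch (normal data, 16 per arm, 0.7 SD).**

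| Correlation | ANOVA interaction | Kruskal-Wallis, end of treatment |
|---|---|---|
| 0.3 | 37% | 44% |
| 0.5 | 51% | 46% |
| 0.7 | 74% | 45% |
| 0.8 | 90% | 43% |

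The two tests reach opposite verdicts in about 39-54% of simulated trials.

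**Step 5. Average cost of the rule.** At correlation 0.7 with about 25% switching, weighting the branches gives 0.75 × 74% + 0.25 × 45% = 67%. Direct simulation gives about 68%, against 74% if ANOVA is always used.

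**Step 6. How much is due to switching itself?** Replace the fallback with a rank test on change from baseline. The whole procedure then has about 73% power against 75% for always using ANOVA (correlation 0.7), and 50% against 51% (correlation 0.5). Most of the loss in Step 5 therefore comes from a fallback that ignores baseline.

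Simulated figures carry Monte Carlo error of one or two percentage points.

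**The case against.** The strongest reply is that little measurable harm follows. Each branch holds its error rate, and so does the two-stage procedure. A baseline-using rank fallback would nearly remove the power cost. At correlation 0.3 the fallback is the more powerful test. The high switching rate needs six separate checks with any single failure decisive, which the plan does not say. All of this stands, and it limits the size of the point.

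It is also fair that the plan commits without condition to analysing the interaction, and that the Randomization, allocation concealment, and blinding section gives data analysis to a separate researcher. The first does not help if the branch taken has no interaction term. The second reduces the room for steering but does not fix the branch, and the text does not say that this researcher is masked to group.

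A reader might infer more than the document supports:
- **Inflated false positives.** Rejection by either test under no effect is about 9-10%, but that bound would require choosing the branch after seeing both results, which the plan does not propose.
- **A check on the wrong quantity.** The text speaks only of normality of the data. It does not exclude residuals, and the detail of the check may properly sit in an analysis plan.
- **A contradiction with the abstract.** An abstract condenses. Naming one branch there is at most an incomplete description.

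Nor can the point be set aside as detail for an analysis plan. The article states the data-dependent rule itself.

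**Conclusion.** The point holds as one about an unfixed primary test. The stated rule lets the collected data choose between two tests of different questions for manometry pressure, and one branch cannot deliver the interaction that the plan promises.

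Its size is a range. Under Shapiro-Wilk at 5%, an unneeded switch on normal data happens in about 5% to 27% of trials. The effect on power runs from a gain of about 7 points (44 − 37) at correlation 0.3 to a loss of about 47 points (90 − 43) at 0.8, given that a switch occurs. At correlation 0.7, averaged over about 25% switching, the loss is about 6 points (74 − 68). A general claim that switching loses power is not supported, because the document gives no correlation. Much of any loss belongs to the unsuitability of Kruskal-Wallis for repeated measures; if that is raised as its own point, the loss should not be counted here as well.

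This should be corrected before the data are analysed. It is not evidence that the trial's error rate is wrong.

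**What to change.** In the Statistical analysis section, remove the normality condition for the primary outcome. State that manometry pressure in cmH2O will be analysed by one named repeated-measures model, that its time-by-group effect is the primary test, and that this holds whatever a normality check shows. Pre-state one sensitivity analysis, a permutation or bootstrap version of the same comparison.

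For secondary outcomes, assign methods by scale type in advance: for example, the same model for continuous scores and an ordinal or rank method for the between-group comparison of the Modified Oxford grade.

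The cost is a few sentences and one extra sensitivity analysis, with no change for participants or data collection.
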